	**-> Final analysis of the primary clinical endpoint: Evaluation of the overall-survival**

1) If a sufficient number of patients consent to randomization, treatment comparison will be performed within the randomized arms. The non-randomized cohort will be used to evaluate the external validity of observed treatment effects according to Schmoor et. al. [11].

2) If a sufficient number of patients cannot be randomized, all recruited patients will be analyzed. Descriptive comparison of treatment groups will be performed for all baseline variables. All analyses will be performed with adjustment to baseline variables affecting survival. Results will be interpreted with respect to any group differences in baseline variables. This study setup was first described by Schmoor et al. as a comprehensive cohort study design [13].

## Outcome measurements

The primary analysis will be an intention to treat analysis on the randomized subjects.

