## Methods/Design

### Study Design

The study is designed as a non-blinded, prospective, randomized controlled clinical trial. Study approval was given by the Ethics Committee of the State Medical Council of Rhineland-Palatinate, Germany [Ref. No: 837.148.03 (3810)]. As part of the Johannes Gutenberg-University, the Coordination Center for Clinical Trials (KKS Mainz, Germany), will monitor the study progress and assure data accuracy. Obvious side effects of radiation therapy render blinding of patients and examiner impossible.

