### Randomization and Sample Size

The present study design consists of a two-armed, randomized controlled trial (RCT), but patients who refuse to participate in a randomized approach and who express a radiation preference will be included in a prospective observational study after giving informed consent. This parallel observational trial will follow the same treatment and observation protocol as the RCT. Patients who agree to the randomized trial will be randomized and stratified according to lymph node therapy (yes/no) as formulated by the DOESAK [12]. Randomization to the radiation group and control group will be done 1 to 1, with recruitment extending over a period of 4 years and ongoing, annual follow-up continuing until the trial ends, i.e. for at least 5 years for each patient. Sample size calculation will be performed for the two-sided log rank test at a significance level of 5%. Assuming exponential distributed survival with 45% survival within the control group and 55% within the radiation group after 5 years (as per results observed in the DOESAK collective), and a drop-out rate of 5% per year, 280 patients per group are required to detect a difference of 5% in overall survival with a power of 70%. To ensure proper power adjustment, an intermediate analysis of the true drop out rate will be conducted. Recruitment of at least 280 patients per group in the observational study will be pursued only in the unfortunate event that patient recruitment within the randomized trial fails.

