### Analysis of RCT and observational trial

Carrying out this RCT is only justifiable if there is a realistic chance of enrolling enough patients to complete a meaningful statistical analysis. Therefore, an intermediate assessment of the randomized patient population will be performed after the first and second years of recruitment. If the numbers are deemed to be insufficient, additional study sites will be added and a web-based information platform will be launched in the hopes of garnering additional attention from affected patients and physicians.

If less than 5% of patients agreed to randomization within the first year and less than 10% within the second year, the RCT will be stopped and continued solely as an observational trial (see Table 1). Due to the dual study design (parallel RCT and observational cohort), the following analysis scenarios are possible:

**Table 1 T1:** Time Schedule

Start	-> Start of recruitment phase (presumably Sep. 2009)
End of year 1	**->**Intermediate assessment of recruitment level:
	- If fraction of randomized patients <5% of total count: ongoing recruitment, else abortion of randomization

End of year 2	**->**Second intermediate assessment of recruitment level:
	- If fraction of randomized patients <10% of total count: ongoing recruitment, else abortion of randomization

End of year 4	**-> End of recruitment phase**

	-

Year 5+6	**->**Follow-up
Year 7+8	
Year 9	
End of year 9	**-> End of Follow-Up**

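### The primary population is fixed as the randomised patients in one place and made to depend on an undefined 'sufficient number' in another, so it is undefined for a trial that keeps randomising but ends below 560

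*Protocol article*

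**What the plan says.** The protocol article makes three kinds of statement that bear on who is in the main comparison.

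- **Unconditional.** Outcome measurements: "The primary analysis will be an intention to treat analysis on the randomized subjects".
- **Conditional.** The two numbered scenarios in Analysis of RCT and observational trial: "If a sufficient number of patients consent to randomization, treatment comparison will be performed within the randomized arms"; and "If a sufficient number of patients cannot be randomized, all recruited patients will be analyzed". The second scenario adjusts for baseline variables that affect survival and asks for interpretation in the light of group differences.
- **Recruitment rules.** The text of the same section stops randomisation if "less than 5% of patients agreed to randomization within the first year and less than 10% within the second year". Table 1 gives the year-1 check as "If fraction of randomized patients <5% of total count: ongoing recruitment, else abortion of randomization", and words the year-2 check the same way with 10%. Randomization and Sample Size adds that "Recruitment of at least 280 patients per group in the observational study will be pursued only in the unfortunate event" that randomised recruitment fails, without saying what counts as failure.

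Study Design describes the trial as open label: "The study is designed as a non-blinded, prospective, randomized controlled clinical trial". Table 1 puts the final analysis at the end of year 9, after recruitment closes at the end of year 4.

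**The concern.** The randomised comparison and the all-patient comparison answer the question with different strength. The first is protected by randomisation. The second mixes it with patients who chose their own treatment, and the Discussion itself expects a strong preference effect. Which of the two is the trial's main result decides whether the trial delivers randomised or observational evidence, so that should follow from one stated rule.

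Here two rules are stated and they part company whenever randomisation falls short. The word that should separate them, sufficient, has no number, no date and no named decision-maker. A self-selected comparison could then displace a randomised one, and the nominal 5% error would no longer be assured.

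**Working it through.** **1. The statements side by side**

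| Outcome of recruitment | Outcome measurements | Numbered scenarios |
|---|---|---|
| 560 randomised | randomised patients | randomised arms (agree) |
| Randomisation stopped under the text rule | randomised patients | all recruited patients, on the natural reading (differ) |
| Randomisation continues, total below 560 | randomised patients | depends on an undefined sufficient number |

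The third row is the gap. The 5% and 10% figures do not fill it: they are fractions of patients recruited, checked at years 1 and 2, and their stated consequence is that randomisation stops. Because text and Table 1 run in opposite directions, even the second row has no single trigger.

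**2. Reproducing the plan's own sample size**

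Inputs (Randomization and Sample Size; Follow-Up): 5-year survival 45% and 55%, exponential; drop-out 5% per year; 4 years' recruitment; follow-up 5 to 9 years; two-sided 5% log-rank test; 280 per group; power 70%. Uniform accrual is assumed.

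- Hazards: λ0 = −ln(0.45)/5 = 0.1597; λ1 = −ln(0.55)/5 = 0.1196. HR = 0.749, ln HR = −0.2894.
- Drop-out hazard: η = −ln(0.95) = 0.0513.
- Probability of an observed death, with t = λ + η: (λ/t) × [1 − (e^(−5t) − e^(−9t))/(4t)]. This gives 0.579 (control) and 0.484 (radiation), mean 0.5315.
- Events at 560: 560 × 0.5315 = 297.6. Schoenfeld requires 295 and Freedman 299 for 70% power, which is 278 or 282 per group against 280 stated.

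The sample size reproduces, on the 45% against 55% difference.

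**3. Power of the randomised comparison at smaller totals**

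Power = Φ(√d/2 × 0.2894 − 1.96), with d = 0.5315 × N.

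| Randomised | Events | Power |
|---|---|---|
| 112 | 59.5 | 20% |
| 280 | 148.8 | 42% |
| 560 | 297.6 | 70% |

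These figures are context. They show how weak the randomised result could be, and so how strong the pull towards the larger population; they do not measure the ambiguity.

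**4. Error if either population were accepted**

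Assume the null is true, there is no confounding, and significance in either analysis is accepted. Let f be the randomised share of all patients (taken as the share of events). The all-patient statistic is √f·Z(rand) + √(1−f)·Z(non-rand), so its correlation with the randomised statistic is √f. The error is P(|Z(rand)| > 1.96 or |Z(all)| > 1.96).

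| f | Correlation | Error |
|---|---|---|
| 10% | 0.316 | 9.5% |
| 25% | 0.500 | 9.1% |
| 50% | 0.707 | 8.3% |

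**5. Confounding, for illustration**

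Suppose residual confounding shifts the log hazard ratio by 0.1 in non-randomised patients, with 297.6 events overall (560 recruited in total). Neither figure is in the article. The all-patient statistic then shifts by (1−f) × 0.1 × √(297.6/4). At f = 25% this is 0.75 × 0.1 × 8.63 = 0.65, and the two-sided error of that analysis alone is about 10%. At f = 10% it is about 12%, and at f = 50% about 7%.

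**The case against.** The passages can be read together. The sentence that introduces the two scenarios comes directly after the stopping rule, so the second scenario may simply be the analysis for a trial whose randomised part has been stopped. The Conclusion's description of the observational study as a backup points the same way. On that reading the switch is driven by recruitment in years 1 and 2, which does no harm to the error rate, and the statement under Outcome measurements is the default otherwise. The label primary is attached only to the randomised analysis, and the second scenario is worded cautiously. A cut-off could also sit in an analysis plan or full protocol not shown here.

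Much of this is fair. But the scenarios turn on a sufficient number, not on whether randomisation was stopped, and nothing equates the two. The all-patient analysis is set as the alternative to the randomised treatment comparison and concerns survival, so it stands in for the main result whether or not it is called primary. A missing cut-off might be left to another document; two conflicting statements in this one are not cured that way.

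Three stronger readings are tempting and are not supported:

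- *That the choice will be made at year 9 with both results on the table.* Year 9 is only when the final analysis falls. The article does not say when the scenario is chosen.
- *That the undefined range is the likely one.* The only consent benchmark, 6.4% in the breast cancer study cited in the Discussion, lies below the 10% check, where the text version of the rule could stop randomisation.
- *That the error approaches the 9.75% of two independent tests (1 − 0.95²).* The all-patient analysis contains the randomised patients, so the tests are correlated and the error is lower.

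Nor can the undefined range be given a lower limit in patients: 10% is a share of total recruitment, which the article does not state.

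**Conclusion.** The point stands as a conflict between two stated rules, with an undefined primary population when randomisation continues but ends below 560. It is more than missing detail, because it settles what kind of evidence the main result is.

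Its size is conditional. If significance in either population were accepted, the two-sided 5% error would be about 8.3% to 9.5% for 50% down to 10% randomised, assuming no confounding; preference-driven confounding would add to it by an amount the documents do not allow one to fix. The article does not say that the choice will be data-driven. It leaves that possible, in a trial where treatment is known to all.

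**What to change.** 1. Reconcile Table 1 with the text of Analysis of RCT and observational trial, so that the stopping of randomisation has one meaning. Settle at the same time whether both yearly checks must fail, since the text joins them with 'and'.
2. State, in the same words in the scenario list and under Outcome measurements, that intention to treat on randomised patients is the primary analysis unless randomisation was formally stopped under that rule, whatever the final number, with the all-patient analysis supportive. If randomisation was stopped, the adjusted all-patient analysis is the main one, is reported as observational, and the randomised subset is shown separately.
3. Record which scenario applies by the end of recruitment (year 4), before any survival comparison by arm.

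The cost is a few sentences and one table correction, with no change to recruitment or data collection; the comprehensive cohort design is kept. The real downside is that a small randomised trial would report a wide interval as its primary result: with 112 randomised, power is about 20%.

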### Primary clinical endpoint

Overall survival at the end of the study

### Secondary clinical endpoints

#### Incidence of tumor relapse

- Time to occurrence of lymphatic metastases

- Time to occurrence of local relapse

- Time to occurrence of distant metastasis

- Tumor related death due to local tumor progression or metastatic spread

#### Life quality

◦ Time to provisional orofacial rehabilitation

◦ Time from operation to first intermediate prosthesis intake

◦ Time from operation to definitive prosthesis application

◦ Life Quality report (EORTC QLQ-C30 with H&N 35 module)

### Metabolic factors

Since the patients involved have equal tumor states, immunohistological investigation of protein expression levels of paraffin embedded sections may help to establish surrogate parameters of radioresistance in oral squamous cell carcinoma. The following factors are to be considered: ki-67, GLUT-1, Hif-1alpha, MCT-1, p53-family members, RB/p130, adhaesion molecules, cytokine and cytokine-receptor expression (IL-2/IL2R_), eIF4E. Pathohistological evaluation of tumor host interaction will be described by vessel density, amount of infiltration by dendritic cells and macrophages, and chain expression in TIL, Fas/FasL-Expression.

### Statistical analysis

Overall survival will be evaluated using a Cox proportional hazard model with treatment and adequate lymph node therapy (yes/no) as covariates. Further covariates may be considered if they affect survival. Statistical analysis will be done with SAS and SPSS^® ^(Statistical Package for Social Science) software for Windows (Chicago, II USA). The Institute of Medical Biostatistics, Epidemiology and Informatics (IMBEI) at the University Medical Center of the Johannes-Gutenberg-University Mainz will provide advice for statistical analysis.

## Discussion

Randomized (blinded) clinical trials represent the gold standard for comparison of treatment efficacy as postulated by the criteria of modern evidenced based medicine [14]. Therefore, RCTs are desired to establish "Grade A" treatment recommendations. A key advantage of randomization is the equal distribution of known and unknown confounding variables within intervention groups, and the elimination of their influence on the outcome [15]. Only the experimental design of a RCT reduces the otherwise unavoidable risk of selection bias and systematic differences which are not induced by the treatment itself, but may affect the outcome. Thus, the study described in this paper could provide a reliable, unbiased appraisal of radiation effectiveness. However, field experience from studies with strongly differing therapy regimens have shown that randomization might fail due to a strong preference of patient and/or physician for a certain therapeutic option (preference effect) [15-17]. Within the "German Breast Cancer Study Group" (GBSG) which investigated operation vs. radiation, only 6.4% of eligible patients consented to randomization [18,19]. Conducting such a study as RCT might not be suitable as a source of evidence due to essential loss of statistical power. External generalization of such data might be harmful if comparison to the intended target population is not supported by a sufficient patient count. Unfortunately the magnitude of the preference effect can not be estimated in advance, although its occurrence in the present study is highly probable due to similarities to the German Breast Cancer Study Group. Thus, the present study setup also uses a comprehensive cohort design. In the unfortunate event that the study fails as a RCT, the obtained clinical data will still allow careful evaluation of radiation effectiveness under controlled conditions in specialist centers. Furthermore, this valuable clinical data might serve as a useful guide for the design of controlled clinical trials in the future. Using a comprehensive cohort design, Rauschecker et al. enrolled more than 1000 patients within the "German Breast Cancer Study Group" (GBSG), and presented a valuable outcome after a long observational period [19].

Further key methodological aspects included differing therapeutic regimens between the study centers, as varying surgical strategies may result in a performance bias with influence on the outcome [20]. The variability of surgical procedures in the head and neck area for control of loco-regional relapse and lymph node involvement is high [21,22]. Thus balanced randomization with stratification by the surgical treatment recommendations of Bier [12] serves for additional improvement of internal validity. In addition, radiation therapy is a well established subsequent therapeutic option for patients with advanced head and neck cancer, whereas a positive effect for the T_1-2_N_1 _neck is still open to evaluation [7]. Similar to surgery, diverse radiation protocols and additional physical considerations necessitate a singular treatment center to ensure quality control as crucial aspect of quality assurance for the present study.

## Conclusion

Under the constraints of a rare condition (pN1) and two substantially differing therapy arms, the practicality and obtainable evidence of a classical randomized study are challenged. The concept of a "Comprehensive Cohort Design" includes the option of a randomized study with an observational study as a backup if randomization of patients fails due to a strong preference effect.

## Abbreviations

OSCC: oropharyngeal squamous cell carcinoma; GBCS: German Breast Cancer Study Group; RCT: Randomized clinical trial; IZKS: Interdisciplinary Center for Clinical Trials; EORTC: European Organisation for Research and Treatment of Cancer; QLQ-C30: Quality of life Questionaire C30; ECOG Index: Eastern Cooperative Oncology Group Index.
